#### Primary outcome measure—exercise capacity

The primary outcome in any eventual trial is expected to be change in exercise capacity following rehabilitation, as measured by the Incremental Shuttle Walking Test (ISWT). The ISWT is a standardised, validated test^16^ of maximal performance and is used as a tool to prescribe the home walking programme. We will estimate a sample size for the subsequent RCT from the observed changes in ISWT in the feasibility study.

The Endurance Shuttle Walking Test (ESWT) will be used to measure endurance exercise capacity and the results of the test are expressed in seconds walked.^17^

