## Introduction

It is estimated that one in four people will develop chronic obstructive pulmonary disease (COPD) in their lifetime^1^ and it is the fourth leading cause of death in the UK. COPD is characterised by a progressive deterioration of debilitating symptoms and increasingly frequent exacerbations. Pulmonary Rehabilitation (PR) has been proven to be effective in improving quality of life, psychological functioning and physical activity and national guidelines recommend that PR should be available to all those who may benefit.^2^ However a survey by the British Lung foundation has found that fewer than 10% of people with COPD have access to such a service.^3^

The standard provision of PR is a supervised package of exercise and education, usually twice a week for a minimum of 6 weeks supported by a home exercise programme. However, some patients find visiting a hospital or community facility very difficult and many programmes report dropout rates as high as 50%. A web-based PR programme has the potential to be a novel and effective approach to increasing patient choice in the mode of delivery and setting of rehabilitation (especially to those patients who decline the offer of conventional PR) while simultaneously increasing the capacity of PR.

There is a growing evidence base for the use of the internet in the management of many chronic conditions in areas as diverse as the management of diabetes, Parkinson's disease, depression, rheumatoid arthritis, asthma, chronic pain and epilepsy.^4–10^ In COPD, Nguyen *et al*^11^ published pilot data on an online dyspnoea self-management programme which had comparable outcomes to a face to face programme but was stopped early due to multiple technical challenges with the online programme.

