#### Sample size estimation and recruitment target

The study will aim to recruit as many suitable patients as are referred to the PR service within the operational phase. One of the main objectives of this feasibility study is to provide data on recruitment and to enable an accurate estimation of sample size for a planned RCT. Based on calculations from previous studies carried out in the PR service, we anticipate a recruitment rate of around 100 patients during our operational phase. This feasibility study will enable us to estimate the required sample size for the subsequent RCT based on a realistic recruitment strategy.

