#### Randomisation

Participants will be randomised into one of two groups: the intervention group who will take part in the web-based PR programme and the standard care group who will undertake conventional PR at the site they were referred to. Randomisation to treatment group allocation will be a 1:1 ratio to either group and will use internet based ‘Sealed Envelope’ randomisation codes where treatment group allocation is sent by automated email to the research physiotherapist.

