#### Quantitative data analysis

As this is a feasibility study, it is not appropriate at this stage to have sufficient statistical power to detect pre to post rehabilitation or between treatment group changes. Therefore for the quantitative data, analysis will primarily be descriptive that is, estimation of means and SDs, proportion of patients eligible/willing to participate in the study. Primary outcome data (ie, the ISWT) will be used to estimate a sample size calculation and non-inferiority margin for a RCT. We will also collect data on drop out and completion rates for both programmes.

Data will be entered and stored on a secure web-based system, REDCAP, which has discrepancy management features. Data can be transferred from REDCAP to the Statistical Package for the Social Sciences (SPSS) for statistical analysis.

All patient information that is collected during the course of the research will be kept strictly confidential. With the patient's permission, their general practitioner (GP) will be informed of their participation in the study and that they may be contacted for relevant reports. Any information about the patient which leaves the hospital will have their name and address removed. Participants will not be identified in any subsequent written material. Results will be reported in such a way that completely preserves confidentiality.

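### The later RCT's sample size and non-inferiority margin are both to come from ISWT changes in a study not powered for them, and the sample size estimate is called accurate without any stated precision

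*Protocol article*

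**What the plan says.** The section on the primary outcome measure (protocol article) names the source of the RCT size: "We will estimate a sample size for the subsequent RCT from the observed changes in ISWT in the feasibility study". The third objective in the Introduction says much the same.

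The section on sample size and recruitment makes this a headline deliverable: "One of the main objectives of this feasibility study is to provide data on recruitment and to enable an accurate estimation of sample size". The strengths and limitations box after the abstract also calls the estimate accurate. The only size given is a throughput expectation: "we anticipate a recruitment rate of around 100 patients during our operational phase". Allocation is equal: "Randomisation to treatment group allocation will be a 1:1 ratio to either group".

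Under Quantitative data analysis, the "analysis will primarily be descriptive that is, estimation of means and SDs", and the authors state that "it is not appropriate at this stage to have sufficient statistical power to detect pre to post rehabilitation or between treatment group changes". The same paragraph then assigns the ISWT data two uses: to estimate the RCT's sample size and to estimate its non-inferiority margin.

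**The concern.** Two statements do not sit well together. The study disclaims the ability to detect ISWT changes within or between arms, yet those same observed changes are to supply the main design inputs of the RCT.

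The margin is the more serious of the two. A non-inferiority margin says how much loss of benefit would be acceptable. That is a judgement about clinical importance, supported by evidence on what conventional rehabilitation achieves. A small two-arm pilot in which both arms receive rehabilitation cannot supply it. If the margin or the target difference followed the observed between-arm difference, chance could set the RCT's main design parameter.

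The sample size is a lesser problem. Taking an SD from a feasibility study is normal practice, but an SD from this many patients leaves a wide range for the required RCT size, and the word accurate tells the reader otherwise. An RCT sized on an SD that happened to come out low would have less power than it states.

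**Working it through.** **Nothing to reproduce.** The figure of around 100 comes from expected recruitment. The article gives no SD, effect, margin, alpha, power or precision target, so the check is on the claim of accuracy.

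**Inputs**
- Recruited: about 100, allocated 1:1, so about 50 per arm (Sample size estimation; Randomisation).
- Evaluable at discharge: not stated. I take 100 (no dropout) and 50 (half lost) as the two ends. The lower end uses the Introduction's remark that "many programmes report dropout rates as high as 50" per cent. That is background on other programmes, so it is my assumption for this study.
- ISWT changes roughly normal, with one SD pooled over two arms, so df = n − 2 (assumption).

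**Step 1: uncertainty in N from the SD alone.** For a fixed difference or margin, required N is proportional to SD². The ratio of the truly required N to the plug-in N therefore has the 95% interval

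df/χ²(0.975, df) to df/χ²(0.025, df),

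which does not depend on alpha, power, margin or the SD itself.

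| Evaluable | df | Lower | Upper | Range for N |
|---|---|---|---|---|
| 100 | 98 | 98/127.28 = 0.770 | 98/72.50 = 1.352 | −23.0% to +35.2% |
| 80 | 78 | 78/104.32 = 0.748 | 78/55.47 = 1.406 | −25.2% to +40.6% |
| 50 | 48 | 48/69.02 = 0.695 | 48/30.75 = 1.561 | −30.5% to +56.1% |

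**Step 2: what that means for power.** The point-estimate SD is below the true SD in 51.9% of repeats (df 98) or 52.7% (df 48). For an RCT planned at 80% power, two-sided 5%, true power is below 70% when the variance estimate is less than [(1.960 + 0.524)/(1.960 + 0.842)]² = 0.786 of the truth. That happens in about 6% of repeats with 100 evaluable, 8% with 80 and 14% with 50.

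**Step 3: precision of the observed between-arm difference.** The 95% half-width in SD units is t(0.975, df) × √(2/n per arm):
- 50 per arm: 1.984 × √(2/50) = 1.984 × 0.200 = 0.40 SD.
- 25 per arm: 2.011 × √(2/25) = 2.011 × 0.283 = 0.57 SD.

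**Step 4: cost of sizing on an upper limit.** The one-sided 80% upper limit multiplies N by df/χ²(0.20, df): 98/86.07 = 1.14 with 100 evaluable, 48/39.62 = 1.21 with 50.

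**The case against.** The strongest reply is that the article does not commit to the worst error. Estimating a sample size from observed changes can mean taking only the SD of change, and the analysis section does speak of means and SDs. In a non-inferiority design the size follows from the margin and the SD, so the observed between-arm difference need not enter. A reader might infer that this difference is to be the RCT's target effect, but no sentence says so. This stands: on the sample size, the text is ambiguous. It does not rescue the margin, which the analysis section says will be estimated from the ISWT data.

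A reader might also take −30% to +56% as the uncertainty at the planned size. The article does not support that. The range needs half the patients to be lost, and retention is something this study sets out to measure. At the anticipated 100, all evaluable, the range is −23% to +35%.

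Nor do the figures show that the RCT would probably be seriously underpowered. A 52% to 53% chance of some shortfall is close to a coin toss and applies to almost any variance estimate. A fall below 70% power is uncommon if retention is good.

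Finally, interval reporting, baseline adjustment and use of an upper confidence limit could sit in an analysis plan that is not shown, or in the RCT's own protocol, and an analysis described as primarily descriptive does not exclude confidence intervals. Their absence here is not a fault. An unseen plan could not, however, make the claim "to enable an accurate estimation of sample size for a planned RCT" true at this size, and it would have to depart from the article to take the margin from elsewhere.

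**Conclusion.** The point holds in limited form. The article draws the RCT's sample size, and explicitly its non-inferiority margin, from ISWT changes in a study it describes as unpowered for such changes, and it calls the sample size estimate accurate with no stated precision.

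Uncertainty in the SD alone leaves the required N between about −23% and +35% of the plug-in value with 100 evaluable, widening to about −30% to +56% with 50. The observed between-arm difference is known only to within about 0.40 SD (50 per arm) or 0.57 SD (25 per arm). These figures assume roughly normal changes and a common SD; the lower number evaluable is an assumption. Use of the feasibility SD for planning is sound. What needs correcting is the source of the margin or target difference, and the unqualified claim of accuracy.

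**What to change.** In the primary outcome and Quantitative data analysis sections, state that the non-inferiority margin or target difference will be justified from outside this study, on clinical importance and external evidence. State that this study supplies only the ISWT SD, reported with its 95% CI, and the observed retention. Show the RCT sample size across that interval and allow for retention. In the sample size section and the strengths and limitations box, replace the word accurate with the expected precision, for example that the SD is expected to leave the required N between about 23% below and 35% above its point estimate with 100 evaluable, and wider with dropout.

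Sizing on an upper confidence limit (×1.14 to ×1.21 at one-sided 80%) or on a baseline-adjusted residual SD is an option that the authors may choose, not a required correction.

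The cost is a few lines of text, with no extra patients, visits or data. The downside is that the stated RCT size becomes a range, and its upper end is larger than the single figure would have been.

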#### Physical activity

This will be assessed using physical activity monitors. The ‘Bodymedia Sensewear’ (APC Cardiovascular, UK) activity monitor is a biaxial accelerometer that can report a number of parameters including step count and energy expenditure. It will be possible to interrogate the data to identify whether individuals accumulate 30 min of moderate activity a day. Following randomisation and prior to starting either programme, all participants will be asked to wear an activity monitor every day for the next week for at least 12 h a day (seven full days). Participants will then be asked to wear the monitor again for another week following the discharge assessment.

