#### Intervention group—web-based PR programme

Following randomisation to the intervention group, patients will be given an appointment to attend an initial session that will introduce the web-based PR programme. At this initial session, the website will be introduced by a PR specialist who is trained in the techniques of motivational interviewing as well as being an expert in PR. Participants will be given a password protected secure login to the website as well as written instructions on website navigation.

The rehabilitation specialist will signpost the patient to all the relevant sections on the website for getting started with the programme as well as going through the home exercise programme and goal setting. There is also an individualised webpage featuring a personalised action plan designed to assist in the management of exacerbations which will be completed by the rehabilitation specialist in conjunction with the patient.

As in conventional PR, patients will be encouraged to exercise on a daily basis at home and record their progress in the online exercise diary section. Throughout the duration of the web-based programme the rehabilitation specialist will be able to review the patient's progress online and communicate with the patient via email or telephone depending on patient preference. There will be weekly contact between the patient and the rehabilitation specialist to ensure that patients are helped to progress their exercise programme appropriately and to answer any queries that arise.

The educational content of the web-based programme is based on the ‘SPACE for COPD’ manual. Patients on the intervention arm of the study will be allowed to work through the website content at their own pace, however, certain milestones need to be completed or achieved before further content can be accessed in order to ensure appropriate progress through the programme. We anticipate from our work with a comparable CR web-based programme ‘ACTIVATE ***YOUR*** HEART’, that it will take approximately 6 weeks to work through the online programme. Patients will then be given an appointment to come into the hospital to attend a discharge appointment once they have completed the programme. The patient is offered a course of conventional rehabilitation classes if they feel it would be more beneficial.

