### Outcome measures

#### Clinical measures

All the measures described below are routinely included in the clinical evaluation of our standard PR programme, with the exception of the use of activity monitors. All measures (except for activity monitors) will be completed at the time of initial assessment for PR by members of the rehabilitation team or at the consent appointment by the research team both who are experienced in these measures. The PR assessment includes information on medical history, medication and baseline demographic data. Standard measures of lung function, level of physical activity, exercise capacity, information needs and health status will be collected.

All measures will be repeated again at the discharge assessment following completion of either rehabilitation programme (usually approximately 6–7 weeks after starting the programme) and will be conducted by a research physiotherapist who will be blind to treatment group allocation.

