#### Physical activity questionnaire

A physical activity questionnaire has been developed at UHL as part of this feasibility study. PACER (the Physical Activity Everday Recall) questionnaire has been designed to capture the everyday physical activities that people do on a regular basis. It asks people to estimate how much time they have spent doing a variety of day to day activities in the past 7 days. Participants will be asked to fill in the PACER questionnaire at the end of the week spent wearing the physical activity monitor. This will occur twice: prior to starting either programme of rehabilitation and again after the discharge assessment on completion of the assigned programme.

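### The first activity-monitor week and first PACER come after randomisation in participants who cannot be blinded, so between-arm change in activity is at risk of bias

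*Protocol article*

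**What the plan says.** The Physical activity section of the protocol article places the first monitor week as follows: "Following randomisation and prior to starting either programme, all participants will be asked to wear an activity monitor every day for the next week". The second week comes after the programme: "Participants will then be asked to wear the monitor again for another week following the discharge assessment".

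The Physical activity questionnaire section ties PACER to those weeks: "Participants will be asked to fill in the PACER questionnaire at the end of the week spent wearing the physical activity monitor". It adds: "This will occur twice: prior to starting either programme of rehabilitation and again after the discharge assessment on completion of the assigned programme". PACER is self-report: "It asks people to estimate how much time they have spent doing a variety of day to day activities in the past 7 days".

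The Clinical measures section gives a different general rule: "All measures (except for activity monitors) will be completed at the time of initial assessment for PR", or otherwise at the consent appointment. It has all measures repeated at the discharge assessment. Only the physiotherapist who does that assessment is described as blind to allocation.

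The Questionnaires section lists a physical activity questionnaire among the additional measures given only after consent. It also describes questionnaires being handed out or posted a week before the discharge appointment and brought back to it.

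**The concern.** A pre-programme measurement serves as a baseline for a randomised comparison only if allocation cannot have influenced it. Here the arms part as soon as the allocation is known: one is booked for a website introduction, the other waits for the next class date. Everyday activity is something a person can change on hearing such news, and PACER asks the person to estimate it. Willingness to wear a monitor for at least 12 hours a day over seven days could also depend on whether the allocation was welcome.

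The article does not say when participants are told. It says only that the allocation is emailed to the research physiotherapist, and it has no step that withholds disclosure until the first week and PACER are finished. It gives no reason for the order.

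At stake is the between-arm difference in change in activity, measured by monitor and by PACER. Activity is a named outcome in the Abstract, and the second objective compares clinical outcomes between the arms. The study exists to inform a later trial, so the order could be carried into it. No analysis plan can reverse the order of collection.

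**Working it through.** **Timing, section by section**

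- First monitor week: after randomisation, before either programme (Physical activity).
- First PACER: end of that week, so also after randomisation (Physical activity questionnaire). The Clinical measures rule excepts only the monitors and would put PACER at the initial assessment or consent appointment. These two conflict.
- Second PACER: after the discharge assessment (Physical activity questionnaire). Clinical measures puts the repeat at the discharge assessment, and Questionnaires describes forms issued a week earlier and returned there. If the physical activity questionnaire named in that section is PACER, the only one described, the final timing is inconsistent as well.

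**Size of a possible bias**

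The plan gives no figure to reproduce on this point. From the documents: about 100 participants anticipated and 1:1 allocation, hence 100 / 2 = 50 per arm. Assumed: SD 1 at both times; true effect 0; a shift d (web minus conventional) of 0 to 0.3 SD in the first week caused by knowing the allocation; pre-post correlation r of 0.5 or 0.7. The documents give neither d nor r.

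- Difference in change scores: bias = −d.
- Difference adjusted for the first week: bias = −r × d.
- Difference in the follow-up week alone: bias from this source = 0.

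Simulated mean differences (5,000 runs per setting):

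| r | d | Change score | Adjusted | Follow-up only |
|---|---|---|---|---|
| 0.5 | 0 | −0.005 | −0.005 | −0.004 |
| 0.5 | 0.1 | −0.099 | −0.049 | 0.000 |
| 0.5 | 0.2 | −0.199 | −0.100 | −0.001 |
| 0.5 | 0.3 | −0.300 | −0.150 | 0.000 |
| 0.7 | 0 | 0.001 | 0.000 | −0.003 |
| 0.7 | 0.1 | −0.100 | −0.070 | −0.002 |
| 0.7 | 0.2 | −0.202 | −0.141 | 0.002 |
| 0.7 | 0.3 | −0.304 | −0.214 | −0.005 |

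These agree with the formulas: at d = 0.2, −r × d is −0.5 × 0.2 = −0.10 and −0.7 × 0.2 = −0.14.

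**Against sampling error**

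The standard error of the change-score difference is √(2 × 2(1 − r) / 50):

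- r = 0.5: √(2 × 1.0 / 50) = 0.20 SD
- r = 0.7: √(2 × 0.6 / 50) = 0.155 SD

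A shift of 0.2 SD is therefore 0.2 / 0.20 = 1.0 to 0.2 / 0.155 = 1.3 standard errors. The bias does not shrink as the sample grows. A shift equal in both arms cancels between arms but still distorts each arm's own change by d.

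The follow-up-only comparison has standard error √(2 / 50) = 0.20 SD, against √(2(1 − r²) / 50) = 0.173 (r = 0.5) or 0.143 (r = 0.7) for the adjusted one. Avoiding the bias at the analysis stage costs some precision.

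**The case against.** The strongest reply has three parts, and much of it stands.

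First, the article shows an opportunity for bias and no more. It does not say when participants learn their arm, and if d is zero there is no bias. This is right, and it rules out saying that the first week is already affected or that the change is biased.

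Second, both first measurements precede the programmes, so the programmes themselves should not contaminate them. A reader might infer that web participants would start early with their online diary. The text does not support that: the login, home exercise plan and goal setting come at the introductory web session, and conventional patients are also given a home programme and a diary. What remains is the effect of knowing the allocation, through anticipation, disappointment, wear or self-report.

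Third, the reach is limited. The analysis is mainly descriptive and unpowered, and the shuttle walk test, which drives the later trial's sample size and margin, is measured at the initial assessment or consent appointment. This also stands. It bounds the point but does not answer it, because activity change remains a reported comparison.

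A reader might also infer that the final monitor week is contaminated by classes taken up after discharge, since "The patient is offered a course of conventional rehabilitation classes if they feel it would be more beneficial". The article does not say when such classes would start, so overlap is possible but not shown. Nor does any section say that the other home-completed questionnaires are filled in after allocation, so the point does not extend to them.

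**Conclusion.** The point holds as a risk of bias confined to change in activity, by monitor and by PACER. The order of collection is explicit, participants cannot be blinded, and no step protects the first measurement from knowledge of the allocation. Size and direction are unknown: the bias is −d for change scores and −r × d after adjustment, with d and r both assumed. Over the assumed range of d from 0 to 0.3 SD, it runs from nothing to 0.30 SD unadjusted and 0.21 SD adjusted. The shuttle walk test, its use for the later trial's sample size, and the recruitment and retention outcomes are untouched. The PACER timing is also inconsistent between sections. The change is worth making, but it does not threaten the study's main purpose.

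**What to change.** Issue the monitor and PACER at or after the consent appointment, and randomise only once the monitor week and PACER are complete. A lighter alternative is to randomise as planned but tell participants their arm only after both are complete.

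If the present order is kept, compare the follow-up week between arms without adjusting for the post-randomisation first week, and state the limitation. This removes only the bias that enters through the first week. Follow-up PACER would still be self-reported by unblinded participants.

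Reconcile the PACER timing, at both ends, across Clinical measures, Questionnaires and Physical activity questionnaire. Optionally, record the dates of any conventional classes taken up after discharge, so that overlap with the final monitor week can be seen.

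The cost is about one week's delay and some losses before allocation. If the wear week precedes randomisation, it may favour compliant patients and alter the apparent willingness to be randomised, which belongs to the first objective. Those losses should be counted separately in the recruitment data; withholding disclosure avoids this effect on randomisation. No new device is needed, but return of the monitor and form must be arranged.
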